#### Recruitment

We will use consecutive convenience sampling to select every person who meets the inclusion criteria based on weekly EHR data reports. This sampling procedure minimizes selection bias (ie, volunteerism) [42]. Using the institution’s local informatics tools [43], we estimated the number of unique patients seen at the eligible clinics in 2016 to be 5200 Black and 13,750 non-Hispanic White patients. Restricting to unique patients with a preventive service encounter in 2016 (a conservative estimate as it excludes patients for whom a preventive exam was not billed, which includes most Medicare patients), there remain over 980 Black and 3725 non-Hispanic White patients who are eligible to participate.

We will contact the participants through a mailed letter or email. The invitation to participate describes the study as “a study to better understand and improve patients’ experiences of care and communication with their doctors.” Research staff will contact eligible participants by phone up to three times to answer questions, encourage participation, and facilitate the completion of the baseline survey. Recruitment will continue until we reach our target sample size of 300. We will collect the survey data using the REDCap system [44] hosted at the academic medical center.

#### Informed Consent

The informational letter participants receive as part of the informed consent process can be found in Multimedia Appendix 2.

#### Intervention

##### EHR-integrated PCD Tool

The Froedtert and Medical College of Wisconsin health network partnered with a digital health company, PatientWisdom Inc, to develop a digital web-based platform to engage with patients ahead of visits. After creating an account on the platform, each participant would be able to provide information about themselves and their situations (ie, PCD) as well as their agenda for the next visit through a mobile and web interface.

The PCD tool is a web-based application running on a Health Insurance Portability and Accountability Act–compliant platform. It has a responsive design that allows for ease of use across a range of devices, from desktops to tablets and smartphones. The tool was codeveloped by the health network, its patients, its clinicians, and an PatientWisdom, Inc. The consumer informatics tool draws upon deep experience and evidence in patient communication [37,45]. The tool invites patients to share *stories* about themselves, their health, and their care. For example, in the *My Self Story* section, patients share what they want their health care team to know about them as individuals, what brings them joy, and about the pressures in their life such as social and personal determinants of health. This section also includes the patient’s health-related priorities and goals and the barriers they experience in achieving them. In addition, in the *My Health Story* section, patients share questions or concerns they want to discuss with the care team, rate their health and provide reasons for the rating, and provide a perspective on how identified health issues affect their lives.

Furthermore, patients identify their preferences toward shared decision making and identify people who support them with health care decisions. Patients can access the application directly through a web address or through a drop-down menu embedded in the patient portal that provides a single sign-on experience for the patient. The latter process makes a direct linkage between the patient and the patient in the EHR. If the patient does not use the patient portal, a statistical matching algorithm links the accounts between the PCD tool and the EHR. After the linkage occurs, clinicians can click on an activity tab within the EHR to view a one-screen summary of the patient’s responses. From preliminary data, average engagement with the tool by patient PCD tool users is approximately 7 min per encounter.

##### EHR Integration

The EHR-integrated PCD tool synthesizes information from the *My Self* and *My Health* stories to create an at-a-glance one-screen view (Figure 2; PCD tool one-screen summary) of the patient, their context, and what is relevant to them. The one-screen summary includes content to facilitate a personal connection and to efficiently grasp goals of care, agenda items, barriers, SDH, styles, and preferences. The 1-page summary highlights elements that the patient recently updated. From preliminary data, clinicians view the summary for approximately 1 min.

As the developers designed the tool to be asynchronous, they established an alert process to flag text and notify clinicians of critical patient data (eg, thoughts of suicide, domestic violence, or distressing symptoms) to guarantee timely interventions [5]. There are plans to transition the alert process to natural language processing once enough PCD are gathered for deep learning.

**Figure 2 figure2:**
[figure not shown]
Patient contextual data tool one-screen summary.

#### PCD Tool Arm

After completion of the previsit survey, all participants in the intervention group will receive an email with a link to the PCD tool for participants to complete their profile. Participants are given the option to complete their PCD profile independently or with assistance from one of the research staff. Providing the participant with options to complete their PCD profile ensures that the participant has access to the internet and a device. Facilitating the enrollment process may also overcome the current rates of adoption and use of the tool (4.7% in 2018) by being responsive to participants’ varying degrees of computer literacy and technical skills.

For participants who do not have an email address and decline to sign up for one, a paper survey will be used to collect the PCD and share them with the health care team at the time of the appointment. Although completion of a paper form loses some of the elements of the trial (PCD not integrated into the EHR), it decreases the chances of adding bias in the study as Blacks are less likely than Whites to have an email account [32,46].

##### Enrollment Process for PCD Tool Facilitation

The facilitation enrollment process includes a description of the PCD tool, followed by the study team member either assisting the participant in registering a PCD tool account using the link to the PCD tool site sent by email or describing how to register a PCD tool account through the patient’s portal. Next, the study team member will review the types of *stories* to share, in the domains of (1) information about me, (2) issues related to my care, (3) my upcoming visit agenda, and (4) barriers to care, to highlight all of them as important pieces of data. In addition, the study team member will share how to upload a picture to the profile. After completing the instructions, the study team member will share that the completed profile would then be available to the care team. The participant can then view how their profile would appear in their EHR via the one-screen summary.

The research team member will document the type of PCD tool facilitation (ie, email link only, over the telephone, or in person) for each participant and take field notes of each facilitation experience. Approximately 1 week before the primary care visit, the research staff will recontact the participant either by telephone or email up to three times. The research staff will thank the participant for being part of the study and inquire if they have questions regarding completing or updating their PCD tool profile. Research staff will also remind the participant to complete the profile, if it is not yet finished.

#### Usual Care Arm

Participants randomized to the usual care arm will complete their previsit survey, scheduled primary care visit, and postvisit survey. The only information regarding the PCD tool they receive before their visit is the email sent automatically by the EHR system to all patients at the academic medical center to create or update their PCD account 1 week before their appointment. For participants who did not have a previsit survey completed at least five days ahead of the appointment, a study team member will give a call to remind the participant to complete the survey as soon as possible. For participants who indicate a preference to complete the previsit survey over the telephone or in person, the study team member will read the survey items verbatim and complete the survey in REDCap.

For both arms, after the scheduled primary care clinic visit occurs, participants will receive up to 3 email reminders to complete the postvisit survey. A study team member will give a call to remind the participant to complete the postvisit survey if it is not completed after the third email reminder. For participants who indicate a preference to complete the postvisit survey over the telephone or in person, the study team member will read the survey items verbatim and complete the survey in REDCap.

#### Data Collection

We will use self-reported surveys to assess the differences in patient-provider communication and patient activation between the PCD tool and usual care arms and by race (Black and White). The primary outcome measure is patient-provider communication assessed using the CAT [37] after the visit. The 15-item measure is unidimensional and has high internal consistency (Cronbach α=.96), with readability at or below an eighth-grade level [37]. The psychometric properties of CAT were tested in a diverse sample. The testing revealed that the instrument has content and construct validity and reliably [37] measures patients’ perceptions of physicians’ interpersonal communication skills. We will examine individual items and the proportion of items with top ratings. The CAT was designed to be administered directly following a visit and is not yet validated in a retrospective context. Therefore, we will use the Clinician and Group Consumer Assessment of Healthcare Providers and Systems (CG-CAHPS) survey [47,48] communication composite questions validated for patients’ perceptions of communication with their provider within the past 12 months as the baseline communication measure. The outcome will be the CAT adjusted for the baseline CG-CAHPS score.

We will use the 13-item PAM [38] to assess changes in the secondary outcome and patient activation, examining the change in pre- and postvisit assessments. Conducted with a nationally representative sample, psychometric testing revealed that the 13-item PAM questionnaire yielded a strong Rasch person reliability score between .85 (real) and .87 (model), and the Cronbach α value was acceptable at .87 [38].

We will collect the following independent variables in the previsit survey: CG-CAHPS communication composite [47], Patient-Reported Outcomes Measurement Information System (PROMIS) Global Health [49], health literacy [50], technology use or technology acceptance [51], and sociodemographic characteristics. We will measure previsit patient-provider communication using the communication composite of the CG-CAHPS survey [48]. The CG-CAHPS communication composite has high internal consistency (Cronbach α=.89) [47], which was determined using a nationally representative sample of over 21,000 patients from 450 US practice sites. We will assess participants’ perceptions of their global health using the PROMIS 10-item Global Health Short Form, which includes scores on global physical health and global mental health. The PROMIS 10-item Global Health Short Form scales had internal consistency reliability coefficients of 0.81 for global physical health and 0.86 for global mental health in a large national survey [49]. Technology use or technology acceptance will be collected using the Health Information National Trends Survey 5, Cycle 1 [51]. Participants will report health literacy using a validated one-item tool [50]. Sociodemographic characteristics and other hypothesized predictors of the outcome measures include income, age, sex, gender identity, health insurance status, educational attainment, number and type of chronic conditions, and length of relationship with primary care provider (in months or years).

We will monitor the use of the PCD tool in 3 ways. First, we will assess whether those in the PCD tool arm completed their profile before their appointment. Second, for participants in the usual care arm, we will determine if they created a profile after they entered the study, as all patients in the academic medical center have access to the PCD tool. Third, we will assess whether any of the care team members reviewed the participant’s PCD tool profile within one day before the appointment and on the day of the appointment. Figure 3 displays the Randomized Controlled Trial Standard Protocol Items: Recommendations for Interventional Trials (SPIRIT) [39] including an overview of study time points, intervention, and assessments of the randomized controlled trial.

**Figure 3 figure3:**
[figure not shown]
Randomized controlled trial Standard Protocol Items: Recommendations for Interventional Trials (SPIRIT).

#### Data Management

The research team will use REDCap for data management [44]. This system is a secure, web-based application designed by Vanderbilt University to support data collection for research. It provides data validation, audit trails, and automated export procedures to a variety of statistical packages. As necessary, branching logic and calculated fields will be created in the system to support data entry.

#### Data Monitoring

The data monitoring committee comprises the study team, the PCD tool’s implementation manager, and the Department of Medicine Safety Committee (DMSC). This pragmatic trial is of low risk, but several monitoring processes are in place to protect the participants. The participants are provided with the study team’s phone number and email address. Participants also have contact phone numbers of members of the ethics review board and can notify the principal investigator (PI) of any harm, which will be reported to the local institution. If a participant shares concerning data (eg, thoughts or actions of self-harm, domestic violence) in their PCD tool profile, the provider is alerted and contact with the participant is initiated. The study team will not conduct interim analyses because of the low-risk nature of the trial. There is an independent process for the DMSC to review all PCD tool data for quality in each quarter.

#### Ethical Considerations

The academic health network’s ethics review board approved the study before enrollment. The study PI will report changes to the protocol to ClinicalTrials.gov, local ethics review board, and all study team members. All study personnel have completed training on the protection of human subjects in research. Data will be stored on a secure server with physical, technical, and administrative access controls using the academic health system–approved REDCap software. Remote access is available over a secure network via encrypted connections to password-authorized users. The media will be kept in locked file cabinets in locked offices. Files with participant identifiers will be stripped of identifiers as soon as they are no longer needed. The study staff have no conflicts of interest. A subsidiary of the affiliated health system has an investment in the company that owns the PCD tool. However, the study staff are not directly employed by the health system nor have any financial ties to the company. There are no provisions for ancillary or postcare of the trial because of the nature of use of the PCD tool, which is currently available to the health system’s patients.

#### Analysis

The trial will evaluate the differences between the arms for change in PAM scores [38] and the CAT score (a postvisit measure) [37], adjusting for the CG-CAHPS score (a previsit measure). The research team will also assess differences in pre- and postvisit patient activation and postvisit patient-provider communication by race. Our primary analysis is an intention-to-treat (ITT) analysis, where every randomized participant is analyzed in the group to which they were randomly assigned [52,53]. Chi-square tests for categorical variables and independent sample *t* tests for continuous variables will be used to examine the differences between the groups at baseline and postvisit. Descriptive statistics (means and standard deviations) will be conducted for the following variables: age, CG-CAHPS communication composite score [47], and PROMIS 10-item Global Health Short Form [49]. Frequencies will be calculated for sex, gender identity, education, marital status, employment status, income, health insurance coverage and type, difficulty paying bills, health literacy, internet use, internet access, internet access location, and internet access device. We will also extract data from each participant’s EHR to calculate their Charlson Comorbidity Index [54] as a measure of morbidity. Previsit assessment of communication using CG-CAHPS [47] as a control variable and postvisit assessment of communication using the CAT [37] will be tested within and between groups using linear regression, controlling for covariates. A linear regression model will be used to determine the factors that predict changes in patient-provider communication and patient activation, controlling for covariates.

However, we expect that there will be some crossover and noncompliance between arms. For example, some individuals randomized to the PCD tool arm may not complete a profile, and some individuals not randomized to enroll in the PCD tool may create a profile. To overcome this limitation, we will conduct additional analyses that account for noncompliance and estimate the effect of the treatment-on-the-treated (TOT) instead of the ITT [55,56]. TOT is sometimes referred to as the local average treatment effect or as a *per-protocol* analysis. We will identify this using a two-stage least squares regression [57,58]. The first stage of the model estimates whether a person used the PCD tool during the follow-up period.

The second stage will identify the causal impact of using the PCD tool on outcomes (patient activation and patient-provider communication). To do this, we will model the predicted use of the PCD tool from stage 1 in the stage 2 model and use the results of this coefficient to interpret how the PCD tool impacts patient activation and patient-provider communication.

A missing value analysis will be conducted on the final data set to determine whether data were missing completely at random, missing at random, or missing not at random [59,60]. To reduce the likelihood of missing data biasing our results, we will use multiple imputation by chained equations to fill in missing data stratified by race [59]. The imputation algorithm will include participant demographics and clinical characteristics. Multiple imputation has been increasingly applied to clinical research to address the common problem of incomplete data sets [60].

For all aims, statistical analysis will be completed using SAS [61] procedures GLM and MIXED to assess and account for possible provider and center heterogeneity. A *P* value of <.05 is considered statistically significant.

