### Study Objectives

In this randomized controlled trial, we aim to evaluate the influence of PCD, collected using a consumer informatics tool, for previsit planning and routine clinical visit discussions with the health care team. The goal is to compare postvisit patient-provider communication and changes in patient activation among patient users and nonusers of the PCD tool, accounting for differences between non-Hispanic White and Black participants (hereafter White and Black). We will measure these constructs using 2 validated measures, the Communication Assessment Tool (CAT) [37] and the Patient Activation Measure (PAM) [38]. Furthermore, we will evaluate the impact by race by determining whether PCD could help mitigate any baseline differences in patient activation and postvisit patient-provider communication between White and Black patients.

We hypothesize that inviting patients directly to submit this information may help with several factors, including activation (patient ready to manage their health and care) and communication (helps prepare perspective and helps the clinician identify salient points).

The primary aims of this trial are to (1) assess the effects of using PCD on patient-provider communication (primary outcome) and patient activation (secondary outcome) and examine whether the effects are different for Black and White patients, accounting for age, gender, and other patient factors and (2) evaluate whether baseline measures of patient-provider communication and patient activation modify the effectiveness of PCD in improving either outcomes, accounting for age, gender, and other patient factors.

We have 2 outcomes of interest: (1) patient-provider communication measured using the CAT [37] and (2) patient activation measured using the PAM [38].

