## Methods

### Study Design

This trial will assess the impact of incorporating PCD on patient-provider communication and patient activation of Black and White participants. The trial is registered at ClinicalTrials.gov (NCT03766841). The health network’s ethics review board approved this trial (registered project PRO00031177). The study protocol adheres to the Standard Protocol Items: Recommendations for Interventional Trials (SPIRIT) 2013 [39] checklist (Multimedia Appendix 1).

Using an experimental study design, we will recruit a prospective cohort of eligible Black and White patients from primary care clinic sites randomized to intervention (invitation to use the PCD tool with facilitated enrollment) or usual care (invitation to use the PCD tool only) and administer questionnaires at baseline and after their primary care visit. The questionnaires assess the perceptions of visit communication and patient activation. The survey results will be adjusted for previsit measures of communication as the CAT [37] is only validated as a postvisit measure of patient-provider communication. Figure 1 presents the randomized controlled trial study design.

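### The comparison of arms on change in PAM does not name baseline PAM as a covariate; adding it gains precision on the secondary outcome at no cost

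*Protocol article*

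**What the plan says.** Patient activation is the secondary outcome, measured with the 13-item PAM before and after the visit. The Data Collection section describes its use as "examining the change in pre- and postvisit assessments", and the Analysis section opens with "The trial will evaluate the differences between the arms for change in PAM scores". A later sentence of the Analysis section adds: "A linear regression model will be used to determine the factors that predict changes in patient-provider communication and patient activation, controlling for covariates". That sentence does not list the covariates.

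Baseline PAM appears as a model term in one place. The second aim, under Study Objectives, is to "evaluate whether baseline measures of patient-provider communication and patient activation modify the effectiveness of PCD in improving either outcomes". It is not named as an adjuster for the comparison of arms.

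The primary outcome is treated differently. The Study Design section explains that "the CAT [37] is only validated as a postvisit measure of patient-provider communication". Study Design, Data Collection and Analysis all therefore say that the postvisit CAT is adjusted for a previsit communication measure, the CG-CAHPS composite.

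**The concern.** When an outcome is measured before and after treatment, a plain comparison of change scores fixes the coefficient of the baseline score at 1. The best-fitting coefficient is usually smaller, so part of any chance difference between arms in baseline PAM is carried into the estimated effect. Stratifying randomisation by race does not balance PAM itself. The result is a wider confidence interval than the same data could give.

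What is at stake is the precision of the PAM result. It is one of the two outcomes of interest, it is to have its own manuscript, and it is also an outcome of the two-stage least squares analysis. The article makes no power claim for PAM, so no stated figure is undermined.

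A smaller point sits in the same section. The sentence on predictors refers to changes in communication as well as in activation. The CAT has no baseline value, and CG-CAHPS is a different instrument that looks back over 12 months. No change on a common scale exists.

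**Working it through.** **The plan's own figures.** The power statements under Sample Size Determination and Randomization concern the CAT only. A two-sided two-sample t test at 0.05 with equal arms (noncentral t) gives 80.4% and 94.0% for 200 participants at effect sizes 0.4 and 0.5. For 250 participants it gives 88.3%, 97.6% and 78.7% at 0.4, 0.5 and 0.35. The stated values are 80, 94, 88, 98 and 79%, so they reproduce. This point does not affect them.

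**Inputs for PAM.** The article gives neither the pre-post correlation r nor the SDs. I assume equal pre- and postvisit SDs (set to 1), r between 0.4 and 0.8, and no other covariates.

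**Variance per participant of the arm contrast**

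- Change score: 2(1−r)
- Adjusted for baseline PAM: 1−r²
- Ratio, adjusted to change: (1−r²) / [2(1−r)] = (1+r)/2, which is below 1 for every r below 1

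The two variances differ by 2(1−r) − (1−r²) = (1−r)². This is the part contributed by chance baseline imbalance: the change-score estimate departs from the adjusted one by (1−r) times the baseline difference between arms.

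| assumed r | change 2(1−r) | adjusted 1−r² | variance ratio | SE reduction, 1−√ratio |
|---|---|---|---|---|
| 0.4 | 1.20 | 0.84 | 0.70 | 16.3% |
| 0.5 | 1.00 | 0.75 | 0.75 | 13.4% |
| 0.6 | 0.80 | 0.64 | 0.80 | 10.6% |
| 0.7 | 0.60 | 0.51 | 0.85 | 7.8% |
| 0.8 | 0.40 | 0.36 | 0.90 | 5.1% |

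**In participants.** Enrolling 300 with the planned allowance of 20% dropout leaves 300 × 0.8 = 240. At r = 0.6, 240 / 0.80 = 300, so 240 analysed with baseline adjustment carry the information of 300 analysed as plain change scores.

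**In power, as illustration only.** The article gives no effect size for PAM. Borrowing its 250 participants and effect size 0.35, in postvisit SD units, power for change against adjusted is 71% against 85% at r = 0.4, 79% against 89% at r = 0.5, 87% against 93% at r = 0.6, and 94% against 97% at r = 0.7.

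**Does the outcome have to be replaced?** No. Write the adjusted model as post = a + τ·arm + β·baseline + error. Subtracting baseline from both sides gives change = a + τ·arm + (β−1)·baseline + error. The arm coefficient τ and the residuals are the same. A simulated data set of 250 confirmed it: τ was 0.532 in both fits, with baseline coefficients of 0.661 and −0.339, which differ by exactly 1. The gain comes from including baseline PAM, not from giving up the change score.

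**The case against.** The strongest case on the other side has four parts.

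- *The PAM analysis is not unadjusted.* A reader might infer from the opening sentence that it is. The article does not support that: it plans a covariate-controlled linear regression for change in activation, both aims account for age, gender and other patient factors, and a usual interaction model for the second aim would contain baseline PAM. This stands. What remains is narrower: baseline PAM is not stated as a covariate for the comparison of arms, and a modifier analysis under the second aim does not settle the first.
- *The list of previsit variables proves nothing.* It begins "We will collect the following independent variables in the previsit survey: CG-CAHPS communication composite" and omits PAM, but PAM had already been introduced as an outcome, and the list is not the full covariate set, since the Analysis section adds the Charlson index. This also stands. The point rests on the stated form of the comparison, not on the list.
- *Covariates may be left to a fuller document.* This stands in part. A condensed article need not give every covariate. But it describes the PAM comparison twice as one of change, and it names the baseline adjuster for the CAT and not for PAM. Naming it is an improvement worth making, rather than the repair of an error.
- *The communication analysis is already right.* A reader might infer from the predictor sentence that it cannot be run. The article does not support that: postvisit CAT with CG-CAHPS as control variable is stated in several places, including just before that sentence. This stands, and only the wording there is off.

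**Conclusion.** The point holds as one of efficiency. The comparison of arms on PAM is specified as change, without stated adjustment for a baseline score that is already collected. Adjusting multiplies the variance by (1+r)/2, which makes the standard error about 16% smaller at r = 0.4 and 5% smaller at r = 0.8. That range rests on an assumed correlation, equal SDs before and after the visit, and no other covariates. Covariates related to baseline PAM would already recover some of the gain.

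It is tempting to go further and call the change-score comparison biased. That does not follow: under randomisation, baseline imbalance and regression to the mean are equal between arms in expectation, and the contrast is valid. Chance imbalance is the source of the extra variance, not a second harm. The primary outcome, its analysis and its power are untouched. The reference to changes in communication is a wording slip.

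**What to change.** In the Analysis section, state that the PAM comparison of arms is a linear regression with arm, baseline PAM, race (the stratification factor) and the other planned covariates. The outcome may be postvisit PAM or change in PAM, since the arm coefficient is the same.

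In the sentence on predictors, replace the reference to changes in communication with postvisit CAT adjusted for CG-CAHPS, in line with Study Design and Data Collection. Leave the main CAT analysis as it is.

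The cost is a few words, and no new data are needed. The article reports that analysis was completed in May 2020. If baseline PAM was not in the model, a refit is simple and should be labelled as specified after the original analysis.
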